### 6.5.2 Premature Termination of the Follow-up for Individual Patients

All such events will be documented in the trial sheets and at the “Prüfzentrum”.

## 7 METHODS OF DIAGNOSTICS AND DATA SAMPLING

### Indirect calorimetry:

Resting energy expenditure will be measured by indirect calorimetry after an overnight fast. This will be performed either by a nurse or a physician, trained and experienced in this procedure. Patients will lie down and rest, once settled down, they will breathe into a plastic hood and oxygen intake and carbon dioxide output will be measured for about 20 min.

### Impedance measurements (Bioimpedance Analysis, BIA):

Using this method, parameters such as body compartments total body water, fat-free mass, body cell mass, extracellular mass and fat mass will be analyzed.

Via MRI scans the development of fat areas (total and relation of subcutaneous and visceral fat) and liver fat content will be investigated. The MRI scan will consist of 48 slices between the upper diaphragm and the femur head and a liver scan. Time required: 30 min

Via Ultrasound, the liver, liver fibrosis (fibroscan) and IMT will be investigated. Time required: 20 min

### Blood sample:

Whenever blood samples are taken, the scientist or another instructed (laboratory) co-worker will be present to ensure proper further sample management (storage, transport etc.). All samples will be sent to the appropriate lab and stored for further examination.

The abundance of serum proteins will be measured by ELISA or Selected Reaction Monitoring based Assays by Linear Ion-Trap Mass Spectrometry (QTRAP 5500). In addition, blood samples will be investigated for glucose, insulin, adipokines, lipids, parameters of inflammation, haematology, biochemistry etc. as mentioned above.

## 8 ADVERSE EVENTS (AE/SAE)

### 8.1 Adverse Events (AE)

#### 8.1.1 Definitions

The Declaration of Helsinki and the ICH-GCP Guideline E6 (point 4.11 and 5.17) set the protection of participants in clinical trials in the first place. Therefore, the safety and harmlessness of interventions and therapies without drugs have to be proved in clinical trials.

**Adverse Events (AE)** are all in patients occurring adverse medical events, unintended disease or injuries or undesirable clinical diagnoses (including abnormal laboratory results), regardless of whether these are related to the investigation or not.

#### 8.1.2 Documentation of adverse Events

All AE's will be documented on the documentation sheet (CRF-page AE), including start and end of the AE, intensity, reason and final result outcome.

Patients will be asked at each visit about AE's and they are also requested to report any to the study management.

In case of Serious Adverse Events (SAE) an AE-sheet including additional SAE-questions will be used.

### 8.2 Serious Adverse Events (SAE)

#### 8.2.1 Definitions

Serious adverse events (SAEs) are according to ICH-Guideline E2A, part IIB defined as follows:

- **results in death,**
- **is life-threatening,**

Note: The term "life-threatening" in the definition of "serious" refers to an event in which the patient was at risk of death at the time of the event; it does not refer to an event which hypothetically might have caused death had it been more severe.

- **requires in-patient hospitalization or prolongation of existing hospitalization,**
- **results in persistent or significant disability/incapacity.**

#### 8.2.2 Documentation of Serious Adverse Events (SAE)

In case of Serious Adverse Events (SAE) an AE-sheet including additional SAE-questions will be used.

### 8.3 Safety Analyses

Each patient is closely monitored for safety during the study period.

### 8.4 Concomitant disease

Any new concomitant disease (except those listed above in 8.1.1.) or worsening of pre-existing concomitant disease will be documented as AE.

## 8.5 Therapeutic Procedures

If a patient requires treatment as a result of an Adverse Event, then it must meet the recognized standards of medical care in order to restore the patient's health. Appropriate resuscitation devices and medication must be available in order to treat the patient as quickly as possible in the event of an emergency.

The action taken to treat the AE/SAE must be documented by the investigator either in the appropriate CRF and/or using additional documents.

## 9 BIOMETRY

### 9.1 Randomisation

The following methods against bias will be applied:

Randomization will be stratified according to:

1. BMI
  - a.  $\geq 27$  to  $< 50$  kg/m^2
  - b.  $\geq 50$  to  $\leq 60$  kg/m^2
2. Current insulin treatment
  - a. yes
  - b. no
3. Sex
  - a. male
  - b. female

The randomization will be performed centrally by the IFB Data Center and will be computer-assisted, using Pocock's minimization algorithm (1). Before start of recruitment, simulations will be performed to demonstrate that the randomisation procedure given the stratification parameters above yields balanced results. A randomisation ratio of 1:1 will be used.

### 9.2 Outcomes

#### 9.2.1 Primary Outcome

- HbA1c values after 1 year

#### 9.2.2 Secondary Outcomes

The main secondary outcomes are:

- T2DM remission rate after 1 year (only for surgical groups)  
Definition T2DM remission: HbA1c  $< 6.5\%$  without indication for anti-diabetic medication
- Weight loss
- General well-being
- Anthropometry (body weight, BMI, WHR (waist to hip ratio), Body fat mass (BIA))
- Clinical parameters (fasting glucose, fasting insulin, fasting c-peptide, HOMA-IR index, serum lipids)

Further scientific secondary endpoints are:

Anthropometric parameter

- Ratio subcutaneous to visceral fat (MRI)

- Intima-media-thickness (IMT) A. carotis com.
- Liver volume, function (ELF-test) and morphology
- Indirect calorimetry

#### Blood parameters

- Serum concentration of GLP1, PYY, GIP, ghrelin (total and active), obestatin, leptin, leptin BP, adiponectin, chemerin, fetuin-A, Nampt, RBP4, Vaspin, OBBP, betatrophin (presently favored to be examined; extra serum will be frozen and stored for potentially new future parameters)
- Inflammatory markers: CrP, WBC, IL-6, TNF $\alpha$

#### Lifestyle parameter

- Average caloric intake per day
- Change in general well-being (SF-36 questionnaire)
- Change in physical activity (IPAQ)

### 9.2.3 Safety Outcomes

Safety will be assessed by tabulating adverse and serious adverse events. A comparison of complications directly related to the interventions will be provided.

## 9.3 Statistical Description of the trial hypothesis

### 9.3.1 Primary Outcome

#### HbA1c

H0: The mean value of HbA1c after 1 year is independent of the treatment arm

HA: The mean value of HbA1c after 1 year depends on the treatment arm

### 9.3.2 Secondary Outcomes

#### T2DM remission

H0: The proportion of patients with diabetes remission after one year is independent of the treatment arm.

HA: The proportion of patients with diabetes remission after one year depends on the treatment arm.

#### Weight loss

H0: The course of weight over time, measured as a percentage of the baseline value, does not depend on the treatment arm.

H0: The course of weight over time, measured as a percentage of the baseline value, depends on the treatment arm.

#### Treatment complications

Estimates for the proportion of procedure related complications will be provided for the treatment arms separately along with confidence intervals.

#### General well-being

H0: The mean SF-36 score after 1 year is independent of the treatment arm

HA: The mean SF-36 score after 1 year depends on the treatment arm

## 9.4 Sample Size Discussion

On the basis of the important trial by Schauer et al. 2012, the HbA1c-levels can be expected to decrease in the pooled surgery groups by 2.9 (1.7) points and in the conservative group by 1.4 (1.5) points. This already takes into account the expectation of lower initial values for HbA1c in our trial, which, however, has almost no effect on the sample size calculation – only the relative difference between arms matters.

Choosing a 5% significance level, 17 conservative and 119 surgical patients have to be analysed using a t-test to reach 95% power for demonstrating this difference. The analysis with ANCOVA will have higher power still. Expecting a drop-out-rate of 15%, 24 + 68 + 68 patients have to be included, to be analysed: 20 + 60 + 60 (control + stRYGB + clIRYGB).

Even with a pessimistic scenario in which the changes in the surgical group are 1.4 points vs 0.4 points with conservative therapy, the ANCOVA analysis still yields a power of 89%.

With the above sample size and pooling the variance between surgical arms, the width for the confidence interval when comparing the two surgical arms can be expected to be smaller than 1.2 percentage points.

## 9.5 Statistical Methods

### 9.5.1 Analysis Population

The main analyses will be performed for the per-protocol (PP) population in all three groups, including the observational arm. Only patients who received the planned treatment and provide data for the primary endpoint will be counted amongst the PP population.

Secondary analyses will be performed for the intention to treat (ITT) population in all three groups, including the observational arm. Missing HbA1c data will be accounted for using multiple imputation. If a patient does not provided data regarding diabetes remission, then this patient will be treated as not having had remission in the analysis.

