# 1 RATIONALE

## 1.1 Medical Background

T2DM is a major burden on public health due to its high prevalence and the association with severe co-morbidities. Good glycaemic control decreases long-term morbidity and mortality. However, HbA1c levels are unsatisfactorily high for many patients. A certain number of prospective trials demonstrated that bariatric procedures (mostly RYGB) can address this problem.

So far, standard RYGB is the operation of choice for most surgeons in metabolic surgery.

However, standardised evidence based limb length recommendations do not exist for the RYGB in bariatric or metabolic surgery.

Due to a longer biliopancreatic limb, the mini-bypass might be better for both weight loss and T2DM improvement, though randomized trials are lacking.

Mimicking this effect, it may be simplest merely to exchange the limb lengths, favouring a long biliopancreatic and short alimentary limb.

Here with a Roux-en-Y reconstruction we do not have the risk of bile reflux into the pouch (and unclear GERD and cancer risk) that are seen with the mini-bypass.

The MetaSurg Study is an open, randomized controlled trial comparing standard RYGB with RYGB with changed limb length and a control arm with standard medical treatment in T2DM patients in a BMI range of 27 to 60 kg/m^2. The primary endpoint is HbA1c improvement after 1 year. The key secondary endpoint for the surgical arms is the diabetes remission rate after 1 year. Diabetes remission is defined as follows: HbA1c <6.5% without any anti-diabetic medication. 68 patients per intervention arm are planned plus 24 patients for the control arm (to be analysed: 60:60:20).

Patients will have a study follow-up of 1 year and further secondary endpoints are weight loss, visceral fat mass, therapy costs and need of medication for other co-morbidities. At our centre, there will be a lifelong follow up with continued data collection.

We expect RYGB with changed limb length to be superior to the standard RYGB with lowest HbA1c levels, a higher diabetes remission rate, relevant weight loss, and higher remission rate of obesity related co-morbidities.

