## **6.5 Premature Termination of the Therapy or Follow-up**

The date (as exactly known as possible) and if possible the circumstances and reasons for every premature termination of the therapy or follow-up will be reported to the KKS-Data Management.

Non-compliance is a common issue in trials. We define non-compliance as significant deviation from the study protocol, specifically missing more than two study visits. All patients, whether compliant or not, shall be followed-up completely.

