### 6.5.1 Premature Termination of the Therapy for Individual Patients

The study participation will be interrupted or terminated if

- the physician decides to
- the patient cannot be reached for more than two missed visits
- if informed consent is withdrawn
- the patient becomes pregnant.

Patients excluded from the study will be reported to the KKS-Data Management. The information will include the date, when known, circumstances and reasons, whether the patient is available for further follow up investigations and whether he/she is available for the routine bariatric follow up or not.

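### The main analysis of a superiority question uses a complete-case per-protocol set, so post-randomisation events decide who counts in the randomised limb-length comparison

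*Protocol*

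**What the plan says.** Section 9.5.1 fixes the lead analysis set: "The main analyses will be performed for the per-protocol (PP) population in all three groups, including the observational arm". It defines the set by two conditions: "Only patients who received the planned treatment and provide data for the primary endpoint will be counted amongst the PP population". The as-randomised set comes second: "Secondary analyses will be performed for the intention to treat (ITT) population in all three groups, including the observational arm". The next sentence adds "Missing HbA1c data will be accounted for using multiple imputation". Because the PP set already requires an observed endpoint, imputation of HbA1c can act only in the secondary analysis.

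The question is one of difference. The alternative hypothesis in Section 9.3.1 is "The mean value of HbA1c after 1 year depends on the treatment arm", and Section 1.1 says "We expect RYGB with changed limb length to be superior to the standard RYGB with lowest HbA1c levels". The protocol gives no non-inferiority margin and no reason for putting PP first.

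Only the two surgical arms are randomised (1:1, Section 9.1). Section 6.3 enrols the control arm without randomisation. Section 9.5.2 gives the surgical comparison special standing: it is tested whatever the global test shows.

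On follow-up, Section 6.5 says "All patients, whether compliant or not, shall be followed-up completely". Section 6.5.1 then opens a list with "The study participation will be interrupted or terminated if". The list includes a physician's decision and a patient who cannot be reached over more than two missed visits.

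**The concern.** Whether a patient receives the planned operation and whether the patient provides a 12-month HbA1c are both settled after randomisation. Either can depend on the arm and on how the patient is doing. Restricting the main analysis to patients who meet both conditions gives up the protection that randomisation provides, in the one comparison that has it.

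The protocol leaves room for such exclusions:

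- Section 6.3 allows up to eight weeks between randomisation and surgery.
- Section 6.3 has patients told their group at once, while Section 3.1 withholds the version of the operation until the trial ends. Whether knowledge of the arm could affect who proceeds is therefore unsettled.
- The planned treatment is a specified pair of limb lengths (Section 5.1), so a patient given another configuration fails the PP definition.

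If the PP and ITT results differ, the plan makes the PP result the headline. Section 1.2.1 aims to bring limb-length recommendations into guidelines, so that headline matters.

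**Working it through.** **Inputs from the protocol.** Section 9.4 gives 24 + 68 + 68 patients to be included, 20 + 60 + 60 to be analysed, a drop-out rate of 15%, a 5% level, and expected HbA1c decreases of 2.9 (SD 1.7) with surgery and 1.4 (SD 1.5) with conservative treatment.

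**The plan's own figure.** For a difference of 2.9 − 1.4 = 1.5, with 17 conservative and 119 surgical patients and a two-sided 5% level (sidedness is not stated, so this is assumed), an unequal-variance t-test has 95.2% power. The stated 95% is reproduced. It concerns pooled surgery against control, not the limb-length comparison.

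**How many randomised patients fall outside the main set.**

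- Surgical arms, by the stated counts: 136 − 120 = 16, and 16/136 = 11.8%.
- All three groups: 160 − 140 = 20, of whom 24 − 20 = 4 are controls who were never randomised.
- At the stated 15% the surgical loss would be 136 × 0.15 = 20.4. The counts and the rate do not quite agree; the counts are used here.

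The protocol does not split the loss into patients not treated as planned and patients without an endpoint.

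**Bias formula.** Let f be the share excluded in an arm, and g the amount by which the mean HbA1c of excluded patients exceeds that of retained patients. The mean over all randomised patients is then the retained mean plus f × g, so the PP mean is too low by f × g. The bias in the difference between arms has size |f₁g₁ − f₀g₀|.

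If the gap h is measured against the whole-arm average instead, the retained mean is too low by h × f/(1 − f).

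**Standard error.** With 60 per arm and SD 1.7: 1.7 × √(2/60) = 0.31. This is unadjusted; ANCOVA should make it no larger.

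**Illustration.** The excluded shares and gaps are assumed; the protocol gives neither. There is no true effect. Type I error is for a two-sided 5% test of this comparison alone.

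| Excluded, stRYGB / cllRYGB | Excluded worse than retained by | Bias (points) | Type I error |
|---|---|---|---|
| 12% / 12% | 1.0 in both arms | 0 | 5.0% |
| 10% / 20% | 1.0 in both arms | 0.10 × 1.0 = 0.10 | 6.2% |
| 10% / 20% | 1.5 in both arms | 0.10 × 1.5 = 0.15 | 7.7% |
| 10% / 20% | 2.0 in both arms | 0.10 × 2.0 = 0.20 | 9.9% |
| 5% / 20% | 2.0 in both arms | 0.15 × 2.0 = 0.30 | 16.2% |
| 11.8% / 11.8% | 0 and 1.0 | 0.118 × 1.0 = 0.12 | 6.7% |

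In the 10% / 20% rows the false advantage goes to cllRYGB. A bias of 0.10 to 0.15 is 0.32 to 0.48 of the standard error. With the gap measured against the arm average, the multiplier is 0.20/0.80 − 0.10/0.90 = 0.139, which gives 0.14 to 0.21 points for gaps of 1.0 to 1.5. The last row shows that equal numbers excluded do not remove the bias if the kind of patient excluded differs.

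**Sections 6.5 and 6.5.1 side by side.** The schedule has four post-baseline visits up to month 12 (Visits 2 to 5). A patient who misses Visits 2, 3 and 4 and cannot be reached has more than two missed visits. Section 6.5.1 then allows participation to end before the endpoint visit, while Section 6.5 wants that patient followed to the end.

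**The case against.** The strongest reply is that the bias may be negligible. Both arms receive a laparoscopic bypass with the same pouch size and exchanged limb lengths, and insurer approval comes before randomisation. Exclusions may therefore be alike in number and kind, and nothing in the protocol supports a 10% against 20% split. ITT with imputation is prespecified as well, so readers could see a disagreement. The sample size is driven by pooled surgery against a non-randomised control, which no choice of analysis set can protect. All of this stands, and it limits the claim to a possible bias of unknown size. It does not explain why the set open to that bias should lead.

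Three stronger readings are tempting and are not supported:

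- A reader might apply 15% to all 160 patients and say that 24 leave the randomised comparison. That total includes 24 controls who are not randomised, and the planned surgical counts give 16 of 136.
- A reader might take ITT with multiple imputation to be unbiased. For missing endpoints that holds only if missingness is explained by the observed data (missing at random). The firm gain is for patients with an observed HbA1c who were not treated as planned.
- A reader might conclude that Section 6.5.1 causes endpoint data to be lost. The section also requires a record of whether the patient is available for further follow-up, and Section 6.3 keeps ineligible patients in follow-up on an intention-to-treat basis. The wording conflicts with Section 6.5, but a loss of data is not shown.

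**Conclusion.** The point holds as a matter of which analysis leads. For a superiority question, with no margin and no reason offered, the protocol puts a complete-case set defined by post-randomisation events ahead of the as-randomised set. About 16 of 136 randomised surgical patients (11.8%) are expected to lie outside the main comparison.

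The documents do not show that the limb-length result will be biased. The bias is nil if exclusions are unrelated to arm and outcome. Under the assumed 10% against 20% exclusion and gaps of 1.0 to 1.5 points, it is a fraction of a standard error; the more adverse assumptions in the table bring it close to one. The point applies to the surgical comparison only. The comparison with the control arm stays open to confounding under either set.

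**What to change.** In Section 9.5.1:

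- Make ITT the main analysis of stRYGB against cllRYGB: all randomised surgical patients in the arm assigned, with observed 12-month HbA1c used whichever operation was received.
- Multiply impute missing HbA1c as already planned, and state the missing-at-random assumption.
- Make PP the sensitivity analysis.
- For the control arm use all enrolled patients, and say that this comparison is non-randomised.

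Reconcile Sections 6.5 and 6.5.1 so that, whatever ends therapy or participation, the 12-month HbA1c is still sought unless consent is withdrawn. This concerns data collection only, not the clinical reasons listed.

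No further patients or visits are needed, since both analyses are already planned. The costs are a slight dilution of the estimate by patients not treated as assigned, and an amendment that may need renewed ethics review under Section 10.3. The change should be made before results are known, because a lead set chosen afterwards would not be credible.

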### 9.5.2 Planned Methods for Analysis

Efficacy: Comparison of the interventions with respect to the HbA1c levels after 1 year

Description of the primary efficacy analysis and population: The primary endpoint will be analysed using ANCOVA for the HbA1c levels, with the baseline value as a covariate and the treatment arm and stratification categories as factors. A closed testing procedure will be used for multiple comparisons. Thus, the three comparisons between the arms will be performed at the nominal significance level of 5% if the global test result is significant. Because the comparison of the surgical groups is of such interest, this comparison will be performed regardless of the result of the global test, though a Bonferroni correction will be used if the global test is not significant.

Secondary endpoint: The comparison of the diabetes remission rates between the surgical arms will make use of a chi-squared-test, and an estimate with 95% confidence interval for the relative probability (“risk”) of remission rates will be provided.

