| Sample size               | 
To be assessed for eligibility: n = 1500
 
To be allocated to trial: n = 160 (plus up to 20 patients in respect of Amendment 5 for additional neurocognitive examinations)
 
To be analysed: n = 140 (plus up to 20 patients in respect of Amendment 5 for additional neurocognitive examinations)
                                                                                                                                                                                                                                                                                                                                                                                                                                                                                                                                                                                                                                                                                                                                                                                                                                                                                                          |
| Therapy                   | 
Experimental intervention: standard RYGB and changed limb length RYGB
 
Control intervention / reference test: control arm with standard medical diabetes treatment in patients who decline surgical treatment or where health insurance rejects the application for it
                                                                                                                                                                                                                                                                                                                                                                                                                                                                                                                                                                                                                                                                                                                                                                                                                                                                                                                                                 |

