#### Observational Control-Group:

All Patients who fulfil the inclusion/exclusion criteria, and

1. admitted to a conservative weight loss programm within the AOP IV-Vertrag in 2016, or
2. received a negative answer of the insurance company to cover the expenses for RYGB or refuse the bariatric surgery and are willing to take part in the study,

will be included in the observational control group (without randomisation).

Examinations will be performed according to the protocol of the interventional groups.

Eligibility of enrolment will be confirmed, and randomisation will be performed at visit 1 (week 0 of the study).

During the enrolment and randomisation visit, the following procedures will be performed

- Obtain medical history, comorbidities, concomitant medication and vital signs and perform physical examination (body weight, BMI, WHR, pulse, RR etc.)
- Routine blood sample (fasting glucose, fasting insulin, fasting c-peptide, HbA1c, serum lipids, Adipokines, inflammatory markers, markers of kidney and liver function etc.)
- Indirect calorimetry (performed either by a nurse or a physician, trained and experienced in this procedure)
- Pregnancy test
- Ultrasound scan (liver, fibroscan, IMT)
- MRI examination by a trained radiologist
- LiMAx test (a functional liver test, will be performed by a medical doctor before and after the preoperative diet)
- BIA-measurement (performed by a trained nurse)
- Diet protocol
- Assess detailed quality of life (SF36) and physical activity (IPAQ)
- Assess Adverse Events since intervention

Whenever blood samples are taken, the scientist or another instructed (laboratory) co-worker will be present to ensure proper further sample management (storage, transport etc.). All samples will be sent to the appropriate lab and stored for further examination.

A detailed description of each procedure is provided in the Working Instructions (WIs).

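### The primary null, global test and only power calculation depend on a non-randomised control arm; the plan analyses surgery versus control like the randomised comparison and adjusts for BMI only at a cut of 50

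*Protocol*

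**What the plan says.** Section 9.3.1 sets one primary null for the trial: "The mean value of HbA1c after 1 year is independent of the treatment arm". Section 9.5.1 puts the observational arm in the main (per-protocol) analysis, so the null covers all three arms.

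The control arm is filled without randomisation. The Synopsis describes standard medical treatment "in patients who decline surgical treatment or where health insurance rejects the application for it". Section 6.3 adds patients from a 2016 conservative weight-loss programme and says that all of these "will be included in the observational control group (without randomisation"). Only the two surgical arms are randomised, 1:1 (section 9.1).

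The primary model in section 9.5.2 is an ANCOVA "with the baseline value as a covariate and the treatment arm and stratification categories as factors". Section 9.1 defines those categories: BMI 27 to below 50 versus 50 to 60, insulin treatment yes or no, and sex. Eligible BMI runs from 27 to 60 (section 4.1).

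Under the closed procedure "the three comparisons between the arms will be performed at the nominal significance level of 5% if the global test result is significant". The same section also tests the two operations against each other whatever the global result, with a Bonferroni correction if the global test is not significant.

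The power statement in section 9.4 is for pooled surgery against control: "Choosing a 5% significance level, 17 conservative and 119 surgical patients have to be analysed using a t-test to reach 95% power". The two operations are given only an expected confidence-interval width.

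**The concern.** The plan makes no distinction between the comparison that randomisation protects and the two that it does not. All three pass through one global test and are then read at the same 5% level, and no section limits how a surgery-versus-control difference may be interpreted. Section 1.2.1 lists demonstrating the efficacy of metabolic surgery among the aims. A reader could take a significant primary test, with its 95% power, as evidence from a randomised comparison.

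The adjustment is coarse where selection may well operate. Section 1.2.1 says that the guideline recommends surgery below BMI 35 preferably within studies, so an insurer's refusal could depend on BMI. Section 4.1 applies different diabetes criteria below 35, which ties BMI to diabetes status by design. In the model, however, a patient with BMI 29 and one with BMI 48 fall in the same BMI category.

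The arms also differ in timing. Follow-up runs from surgery in the surgical arms and from baseline in controls (footnote to the Schedule of Assessments). The 2016 programme patients have a Visit 5 window of 12 (-1; +6) months (section 5.2).

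**Working it through.** **1. The plan's own figure.** Inputs from section 9.4: "decrease in the pooled surgery groups by 2.9 (1.7) points and in the conservative group by 1.4 (1.5) points", so the difference is 1.5 with SDs 1.7 and 1.5; 5% level (taken as two-sided); 17 + 119 analysed.

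- SE = √(1.5²/17 + 1.7²/119) = √(0.1324 + 0.0243) = 0.396
- Non-centrality = 1.5/0.396 = 3.79, Satterthwaite df = 22.3
- Unequal-variance t-test power = 95.2%

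The figure reproduces, and it is wholly a surgery-versus-control calculation.

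**2. What the plan gives the randomised contrast.** Only a width. With 60 per arm, width = 2 × t(0.975; 118) × SD × √(2/60), which is 1.23 at SD 1.7 and 1.16 at SD 1.6. For orientation, the difference detectable with 80% power at SD 1.7 is (1.96 + 0.84) × 1.7 × √(2/60) = 0.87 points. Power for an assumed 0.5 points is 36%.

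**3. How a control shift moves the global test.** Suppose there is no treatment effect in any arm, 20/60/60 patients are analysed, and residual SD is 1.68. If unadjusted differences move the control mean by b, the non-centrality is λ = (20 × 120/140) × b²/1.68² = 17.14 b²/2.82. For b = 0.5, λ is about 1.5. The F test has 2 numerator df.

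| b (points) | 0.25 | 0.5 | 0.75 | 1.0 |
|---|---|---|---|---|
| Global rejection | 7.9% | 17.8% | 35.5% | 58.2% |

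**4. How large b could be from BMI alone.** The protocol gives no BMI distribution by arm and no BMI slope, so these inputs are assumptions: surgical BMI mean 42, SD 6; control mean 5 or 8 units lower; baseline HbA1c with SD 1.5 and slope 0.5; residual SD 1.45. The protocol's ANCOVA was fitted to simulated trials of 20/60/60 with no treatment effect (2,000 runs per setting for slopes 0.05 and 0.10).

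| BMI slope (HbA1c points per unit) | BMI gap | Residual bias | Global rejection |
|---|---|---|---|
| 0.05 | 5 | 0.19 | about 7% |
| 0.05 | 8 | 0.33 | about 10 to 11% |
| 0.10 | 5 | 0.39 | about 12 to 14% |
| 0.10 | 8 | 0.66 | about 33% |

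Bias scales with the slope, so 0.02 per unit gives 0.4 × 0.19 = 0.08 and 0.4 × 0.33 = 0.13 points, with rejection a little above 5%. The ranges in the last column are the spread between separate simulations. The raw shift for a gap of 5 at 0.05 is 0.25 points, of which 0.19 survives; for a gap of 8 it is 0.40, of which 0.33 survives. The cut at 50 therefore removes only about a fifth.

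The rejection rates do not depend on the sign of the slope, but the direction of the bias does. If controls have lower BMI and HbA1c rises with BMI, controls look better and the bias is against surgery.

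**5. The remedy.** Adding continuous BMI to the same model brought the bias to about zero and global rejection back to 4 to 5.5%. The simulated BMI effect was linear, so this shows what the term can do when that form is right.

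**6. The randomised contrast.** In every setting of step 4 its false-positive rate stayed at or below 5%. Its power under the full procedure, for a difference of 0.87 and SD 1.7 (Bonferroni taken as 5%/3, since no divisor is stated), was:

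| Control mean | Direct 5% test | Planned procedure |
|---|---|---|
| 1.5 worse than stRYGB | 79.4% | 79.4% |
| 1.0 worse | 79.3% | 79.1% |
| equal to stRYGB | 79.5% | about 72% |

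**The case against.** The strongest reply is that the design is disclosed: the third arm is called observational throughout, so no careful reader will think it was randomised. The model also adjusts for more than BMI; baseline HbA1c, insulin use and sex remove part of the confounding. Extra covariates are often left to a SAP, and with about 20 analysed controls a long covariate list would be fragile. Much of this stands, and it is why the remedy is limited to one covariate and some wording. It does not answer the point itself, because sections 9.3.1, 9.4 and 9.5.2 fix the null, the powered contrast and the covariates in the protocol.

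A reader might infer more than the documents support:

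- **That surgery could be declared effective purely through confounding.** This is possible in principle but not shown. The most natural BMI scenario biases against surgery. So does forcing one baseline slope on all arms: with assumed slopes of 0.3 after surgery and 0.8 in controls, and control baseline 0.5 or 1.0 lower, a true 1.29 becomes 1.08 or 0.87. The biases in step 4 are also well below the planned 1.5 points.
- **That the randomised comparison is only a follow-on to the global test.** Section 9.5.2 tests it in any case.
- **That the global test costs it power.** The fall to 72% needs controls who do as well as stRYGB, contrary to section 9.4.
- **That all controls are self-selected.** This fits those who refuse surgery. The others are selected by insurer or programme, though they are equally non-randomised.
- **That the primary question must be replaced.** Comparing medical treatment with both operations is a stated aim, and making the surgical contrast the sole primary would leave about 80% power only for a difference near 0.9. That is a trade-off for the sponsor.

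**Conclusion.** The point holds in a limited form. From the text alone, the primary null, the global test and the only power calculation include or target a non-randomised arm, and the analysis section treats those comparisons like the randomised one. A significant global test therefore cannot by itself be read as a randomised treatment effect.

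The BMI part depends on assumptions. Gaps of 5 to 8 units with slopes of 0.02 to 0.05 leave about 0.1 to 0.3 points of bias and global rejection of about 5 to 11% instead of 5%. A slope of 0.10 leaves 0.4 to 0.7 points and about 12 to 33%. Neither the gap nor the slope, nor its sign, is given in the protocol. The comparison of clIRYGB with stRYGB is sound in this respect. This is something that should be fixed; it does not invalidate the trial.

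**What to change.** - **Section 9.5.2, model:** add continuous baseline BMI to the ANCOVA, alongside the stratification factors. BMI is recorded at Visit 1, so no new data are needed.
- **Sections 9.4 and 9.5.2, labelling:** state that surgery versus control is a non-randomised comparison, that the 95% power refers to it, and that a significant global test alone is not evidence of a randomised treatment effect.
- **Section 9.5.2, reporting:** report clIRYGB versus stRYGB as the randomised comparison, with its own estimate and confidence interval.

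The cost is one model term and a more cautious claim against medical care. Continuous BMI does not remove confounding from factors that are not in the model, such as the reasons for refusing surgery, so the labelling is needed as well as the covariate.
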